## Abstract

**Introduction:**

Lower urinary tract symptoms (LUTS) is a bothersome condition affecting older men which can lead to poor quality of life. General practitioners (GPs) currently have no easily available assessment tools to help effectively diagnose causes of LUTS and aid discussion of treatment with patients. Men are frequently referred to urology specialists who often recommend treatments that could have been initiated in primary care. GP access to simple, accurate tests and clinician decision tools are needed to facilitate accurate and effective patient management of LUTS in primary care.

**Methods and analysis:**

PRImary care Management of lower Urinary tract Symptoms (PriMUS) is a prospective diagnostic accuracy study based in primary care. The study will determine which of a number of index tests used in combination best predict three urodynamic observations in men who present to their GP with LUTS. These are detrusor overactivity, bladder outlet obstruction and/or detrusor underactivity. Two cohorts of participants, one for development of the prototype diagnostic tool and other for validation, will undergo a series of simple index tests and the invasive reference standard (invasive urodynamics). We will develop and validate three diagnostic prediction models based on each condition and then combine them with management recommendations to form a clinical decision support tool.

**Ethics and dissemination:**

Ethics approval is from the Wales Research Ethics Committee 6. Findings will be disseminated through peer-reviewed journals and conferences, and results will be of interest to professional and patient stakeholders.

**Trial registration number:**

ISRCTN10327305.

Strengths and limitations of this studyProspective, multicentre study in an appropriate population in primary care.The index tests are tests that can be done routinely in primary care or at home by patients.The diagnostic models developed will be validated in a separate cohort of men from the same population.The assumed prevalence of the three target conditions may be different in practice.Some test results may be missing or difficult to obtain.

## Introduction

Lower urinary tract symptoms (LUTS), such as frequent urination, a slow stream, and having to wake in the night to urinate, affect a significant proportion of older men and can lead to poor quality of life. Three common causes of LUTS are instability of the bladder muscle (detrusor overactivity (DO)), benign enlargement of the prostate gland causing bladder outlet obstruction (BOO) and weakness of the bladder muscle (detrusor underactivity (DU)). These may be present individually or in combination.

The reference standard test for investigation of LUTS, and thus diagnosis of DO, BOO and DU, is invasive urodynamics, which takes place in secondary care. Invasive urodynamics will be conducted rather than video urodynamics, which is in line with most contemporary national and international guidelines, and is sufficient to diagnose DO, BOO and DU, to which most non-complicated adult male LUTS can be attributed. It involves insertion of catheters into the patient’s bladder and rectum so that the behaviour of the bladder and outlet can be examined during filling and voiding. Owing to availability, complexity and cost, management decisions for men with LUTS are usually based on results from a combination of non-invasive and minimally invasive investigations instead. These include digital rectal examination (DRE) to assess prostate size, symptoms questionnaires, uroflowmetry and measurement of post void residual.

National Institute for Health and Clinical Excellence (NICE) guidelines suggest that many men referred to specialist care with LUTS are eventually managed conservatively, and so they could have remained within primary care. Male LUTS account for around four presentations per month in an average-sized general practitioner (GP) practice. This rate of presentation, although high enough to represent a large burden on the National Health Service (NHS), makes it difficult for GPs to gain sufficient expertise to be confident about diagnosis and management. Furthermore, GPs do not have access to simple tools giving an indication of the most likely cause of symptoms to guide treatment and management. Making such a tool available should improve treatment efficacy, standardise treatment, reduce unnecessary referrals, expedite referral of those requiring specialist care and thus improve cost-effectiveness of NHS care.

This led to the National Institute for Health Research (NIHR) releasing a 2015 health technology assessment (HTA) commissioned call (HTA number 15/40) seeking the delivery of: ‘The development of a decision aid to help inform the choice of treatment or need for specialist referral for men presenting with lower urinary tract symptoms in primary care’. Our team was successful in obtaining this funding and here we describe the protocol for our study: ‘Primary care management of lower urinary tract symptoms in men: Development and validation of a diagnostic and clinical decision support tool’ (the PRImary care Management of lower Urinary tract Symptoms (PriMUS) study).

### Aims, objectives and outcome measures

The PriMUS study aims to develop three diagnostic prediction models based on the results of simple clinical tests that can provide a useful prediction of urodynamic observations in men with LUTS. We will assess the diagnostic accuracy of these models, which will be implemented in software, along with management recommendation algorithms to form a clinical decision support tool for use in UK primary care. Our primary and secondary objectives and measures are outlined as follows.

#### Primary objectives

Develop a statistical model to predict the likelihood of three urological conditions (BOO, DO and DU) based on a series of non-invasive index tests, with invasive urodynamics as the reference standard.Estimate the diagnostic accuracy of the above statistical model in an independent validation cohort.

#### Secondary objectives

Develop a series of patient management recommendations and thresholds for clinically useful diagnostic prediction by expert consensus and with reference to current clinical guidelines that map to the diagnoses predicted by the statistical model.Combine the statistical model and management recommendations into an online tool that will form the prototype clinical decision support tool.Complete a qualitative study to explore the feasibility of introducing the clinical decision support tool into primary care including potential acceptability to primary care staff and patients.Collect NHS costs involved in delivering the new pathway and compare with cost of standard pathway calculated from NHS and other sources.

#### Primary outcome

Sensitivity and specificity of the diagnostic models for detecting DU, BOO and DO will be determined. The three conditions will be coded as binary outcomes (present/absent).

#### Secondary outcomes

A patient management algorithm to guide initial treatment for men with LUTS.A prototype online clinical decision support tool for use in primary care.Qualitative summary of patients’ and clinicians’ views on the use of a LUTS clinical decision support tool in the primary care setting.Costs/savings of implementation of the primary care LUTS clinical decision support tool both from a population and individual patient perspective.

## Methods and analysis

### Study design

This is a prospective, diagnostic accuracy study involving the development and validation of a diagnostic tool. An internal pilot will assess primary care recruitment, acceptability of the reference test (invasive urodynamics) and data collection. Two cohorts of participants, one for development of the prototype diagnostic tool and other for validation, will undergo a series of index tests (see table 1) and the invasive reference standard (urodynamics) in approximately 90 GP practices across Newcastle upon Tyne, Wales and Bristol (a list of study sites can be found on ISRCTN). There will also be qualitative data collection to explore acceptability of the urodynamics test and develop management recommendations for the tool and for user-testing of the prototype (see table 2).

**Table 1 T1:** Index tests and input parameters that will be tested for use in the three logistic regression models

Test	Result	Input parameters that will be tested for use in the three logistic regression models (result or unit)
Relevant demographics	Age in years	Age (years)
Physical examination of abdomen	Bladder palpable/not palpable	N/A
Digital rectal examination	Prostate mild/moderate/severe enlargement Further assessment for prostate cancer required/not required	Prostate size (enlarged/not enlarged)
Prostate Specfic Antigen (PSA)	PSA value—established thresholds for further assessment for prostate cancer (typically >3 ng/mL) or benign enlargement (typically ≥1.5 ng/mL). For clinical decision support tool: continuous variable in ng/mL	PSA (ng/mL)
International Consultation on Incontinence Questionnaire Male Lower Urinary Tract Symptoms Short Form	Total score (0–52), voiding symptom score (0–20), storage symptom score (0–24). Individual symptom bother scores scored separately from symptom severity scores (0–130)	Storage/incontinence symptoms subscore Voiding symptoms subscore
International Prostate Symptom Score questionnaires	Total score (0–35)	Storage/incontinence symptoms subscore Voiding symptoms subscore
Bladder diary	Waking (day) time frequency, sleeping (night) time frequency, 24 hours voided volume, daytime voided volume, nocturnal voided volume, average volume voided each void, total urgency scores	Mean urgency score Mean 24 hours fluid intake (mL)
Uroflowmetry (Flowtaker)	Maximum flow rate, voided volume against normal age-adjusted range. Single value in mL/s	Median maximum flow rate (mL/s) Median voided volume (mL) Mean 24 hours frequency Mean nocturia
Post void residual	Residual volume against normal age-adjusted range. Single value in mL	Post void residual volume (mL)

PSA, prostate-specific antigen.

**Table 2 T2:** Secondary substudies

Qualitative studies	Details
**Patient and Clinician Acceptability Interviews—Internal Pilot Phase**	During the pilot phase, we will conduct semistructured qualitative interviews (n=30–40) with patients (consenting and declining entry to the main study) and participating clinicians to assess the acceptability of the urodynamic procedure and the PriMUS study, as part of our progression criteria. Interview schedules will be developed in discussion with clinician and patient representatives of the Study Management Group. Interview guides will broadly explore: practicality and acceptability of conducting urodynamic investigations (and experiences of patient participants); reactions to and experiences of the study processes (including barriers/facilitators). An iterative approach will be taken, so that schedules can be refined to further explore unanticipated themes that arise during data collection. Interview transcripts will be entered into NVivo qualitative analysis software and analysed using Framework Analysis (using key topic areas as the framework).^9^ Data will be used to inform strategies that will maximise recruitment and retention.
Development of Management Recommendations	Algorithms are required to link outputs from the statistical models, which will be likelihoods of each target condition, with patient management recommendations to form the clinical decision support tool. The starting point will be recommendations from the relevant NICE clinical guideline. Qualitative work with urologists will support the development of these management recommendations, through posing a range of clinical case scenarios to urologists using interview and questionnaire methodologies (n=15–20). Urologists will be asked to how they would manage these scenarios, with a focus on thresholds for treatment and strategies for multiple diagnoses.
Tool Feasibility Assessment	The aim of the user-testing phase will be to build on the interviews conducted as part of the pilot phase evaluation to assess GPs’ attitudes and reactions to the prototype clinical decision support tool. GPs (n=10–12) will be sent the tool prior to the semistructured telephone interview and asked to use it. The interview schedule will explore the following: ease of use, content, design and perceived acceptability and feasibility of using the tool in routine primary care settings (allowing succinct exploration of the prototype tool). Interview transcripts will be entered into NVivo qualitative analysis software and analysed using Framework Analysis (using key topic areas as the framework).^9^ Feedback will be used to improve and refine the tool.

GPs, general practitioners; NICE, National Institute for Health and Clinical Excellence; PriMUS, PRImary care Management of lower Urinary tract Symptoms.

### Participants

Adult men who consult their GP with one or more LUTS in UK primary care settings.

#### Inclusion criteria

Men aged 16 years and over.Men who present to their GP with a complaint of one or more bothersome LUTS (this includes men on current treatment, but who are still symptomatic).Men able and willing to give informed consent for participation in study.Men able and willing to undergo all index tests and reference test, and who complete study documentation.

#### Exclusion criteria

Men with neurological disease or injury affecting lower urinary tract function.Men with LUTS considered secondary to current or past invasive treatment or radiotherapy for pelvic disease.Men with contraindications to urodynamics such as heart valve or joint replacement surgery within the last 3 months, or immunocompromised/immunosuppressed men.Men with indwelling urinary catheters or who carry out intermittent self-catheterisation.Men whose initial assessment suggests that clinical findings are suggestive of:Prostate or bladder cancer according to standard NHS cancer pathways. If later deemed unlikely, they become eligible for study participation.Recurrent or persistent symptomatic urinary tract infection (UTI). If UTI is successfully treated but LUTS remain, they become eligible for study participation.Urinary retention, for example, palpable bladder after voiding.Men unable to consent in English or Welsh where a suitable translator is not available.

### Test selection

Test selection, including the reference standard, was informed by a systematic review included in the relevant NICE guideline CG97^1^ updated with a study-specific unpublished selective review by our group in 2015, the judgement of the expert clinical members of the study team and the stipulations of the funding commissioning brief. All participants undergo all tests that are a combination of:

Tests carried out for eligibility assessment prior to enrolment, as described earlier.Tests carried out at participant visits to a primary or secondary care location for the purpose of the study following enrolment.Tests carried out by the participant at home following enrolment.

### Index tests

Twelve potential parameters will be considered for the three logistic regression models. The investigations that provide these parameters are described in table 1.

### Reference standard

Our reference standard is invasive urodynamics, a test routinely carried out in a specialist care setting for the investigation of LUTS. For this study, it will be performed using portable equipment (Goby, Laborie, Mississauga, Canada) in either a primary or secondary care location, by specially trained urodynamic nurses, according to International Continence Society standards.^2^ Safety information is covered in the Safety and pharmacovigilance section.

### Study procedures

#### Data collection

GPs, primary care nurses or an appropriately trained delegate will undertake the data collection related to all the index tests. Specialist-trained urodynamic nurses will undertake the data collection for the reference test.

#### Data management

All data collection will be done by electronic data capture using a bespoke database developed by the Cardiff University Centre for Trials Research Clinical Trials Unit (CTR), and paper copies of all case report forms will be available.

#### Identification and screening

All men will be identified either opportunistically during a GP consultation or by regular, predefined primary care database searches. They must undergo three screening tests prior to enrolment into the study: a physical examination of the abdomen (palpable bladder check), DRE and prostate-specific antigen test. The latter two test results are accepted if they have undergone these investigations within the last 6 months.

#### Informed consent

Informed consent will be obtained in the first study visit (Study Visit Part A) prior to any study procedures by those suitably trained and on the delegation log. Eligible patients will be given time to consider before being asked to sign the consent form. Once consented, participants will be allocated a unique study number (participant ID).

Separate informed consent will be taken for participation in the qualitative data collection.

#### Withdrawal

Patients will be notified that they can withdraw consent for their participation in the study at any time during the study period.

#### Study Visit Part A

Once informed consent is obtained, the remaining index tests will be collected. These include a baseline assessment (collecting demographic information, relevant medication and medical history) and two self-reported questionnaires: International Prostate Symptom Score and International Consultation on Incontinence Questionnaire. Participants will be given the bladder diary to complete for 3 days at home and instructed to bring it during their invasive urodynamic visit (Study Visit Part B).

#### Study Visit Part B—reference standard

On arrival, the patient will be asked to pass urine into a flowmeter in private, after which a measurement of post void residual ultrasound (one of the index tests; see later) will be made. A dual lumen catheter (one channel to fill the bladder and the other to measure intravesical pressure, P_ves_) will be inserted into the bladder via the urethra, and a single lumen catheter will be inserted into the rectum to measure abdominal pressure (P_abd_). Detrusor pressure (P_det_), generated by the bladder muscle itself, is calculated by subtracting P_abd_ from P_ves_.

#### Filling phase

The patient will be asked to bring their completed bladder diary (one of the index tests; see earlier) to their urodynamics appointment, providing the urodynamic nurse with an indication of their maximum bladder capacity. The patient’s bladder will be filled with sterile saline at a maximum rate of 50 mL/min. They will be asked to report the first sensation of bladder filling, followed by the point at which they feel the normal desire to void and finally the strong desire to void. At this point, bladder filling will be stopped and provocation, in the form of running taps and asking the patient to cough, will be performed.

#### Voiding phase

Following provocation, the patient will be given permission to void, marking the start of the voiding phase. Voided volume (V_void_) and flow rate (Q) will be measured as they pass urine into the flowmeter.

If either the filled or voided volumes are below 150 mL, the filling and voiding phases will be repeated once more using a maximum filling rate of 20 mL/min.

#### Diagnostic definitions

Definition of our three target conditions will be based on the following parameters measured during invasive urodynamics and subsequently read from a graphical representation of the test:

Maximum detrusor contraction pressure during the filling phase.Maximum flow rate during the voiding phase (Q_max_).Detrusor pressure at the point of maximum flow rate (P_detQmax_).

If there are no detrusor contractions during filling, DO is not present. If there are any contractions (contraction pressure >0), DO is present.

Diagnosis of BOO is based on the BOO index (BOOI), defined as P_detQmax_−2*Q_max_. BOO is present if BOOI >40 and absent if BOOI ≤40.

Diagnosis of DU is based on the bladder contractility index (BCI), defined as P_detQmax_+5*Q_max_. DU is present if BCI<100 and absent if BCI≥100.

##### Debrief process and monitoring process

The urodynamic nurses will debrief the patient following the urodynamic procedure providing them with a post-urodynamics leaflet and safety card. The urodynamic nurse will also instruct the patient that they will receive a 3-day follow-up phone call to monitor for any related adverse events.

#### 3-day follow-up phone call

The urodynamic nurses will contact the patient 3 days (with flexibility if phone call falls on weekend) after their urodynamic procedure to monitor for any adverse events and serious adverse events (SAEs). Any SAEs are subsequently recorded by the urodynamic nurses and processed centrally by CTR. This process is outlined in the Safety and pharmacovigilance section (see later).

#### Review process

Invasive urodynamics is a complex investigation and interpretation can be challenging. Furthermore, since standard practice involves interaction between the reference and some index tests as described earlier, their primary interpretation in this study is not blinded. Therefore, a review process will be implemented to ensure the integrity of the reference standard. All studies will be second-read by a blinded reviewer to extract the three parameters described earlier. If any of the resulting diagnoses differ between the nurse and this reviewer, the case will go to a second non-blinded reviewer who makes the final decision.

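### Disputed urodynamic diagnoses are settled by a non-blinded reviewer, so the blinded second read cannot prevail alone and sensitivity and specificity are at risk of being overstated

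*Protocol article*

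**What the plan says.** All of this is in the protocol article. Under Review process it concedes that "since standard practice involves interaction between the reference and some index tests as described earlier, their primary interpretation in this study is not blinded", and for that reason "a review process will be implemented to ensure the integrity of the reference standard". The safeguard is a second reading: "All studies will be second-read by a blinded reviewer to extract the three parameters described earlier". Where the two readings lead to a different label on even one of the conditions, "the case will go to a second non-blinded reviewer who makes the final decision".

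Two index tests are tied to the urodynamics visit. Under Study Visit Part B, before the catheters are placed, "a measurement of post void residual ultrasound (one of the index tests; see later) will be made". Under Filling phase, men are asked to "bring their completed bladder diary (one of the index tests; see earlier) to their urodynamics appointment", where the nurse uses it to judge bladder capacity. Table 1 lists post void residual volume, mean urgency score and mean 24-hour fluid intake among the candidate model inputs.

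Diagnostic definitions derives the labels from values read off the trace: any contraction during filling for DO, BOOI above 40 for BOO, BCI below 100 for DU. Primary outcome makes sensitivity and specificity against these labels the main result, and the Validation cohort paragraph sets 75% as the minimum useful level.

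**The concern.** The blinded read was added to repair an unblinded one, yet the discordance rule returns the decision to an unblinded reader whenever the blinded read makes a difference. If knowledge of the residual or the diary sways a doubtful reading, the outcome comes to contain part of the predictors (diagnostic review bias). A model using those predictors would then look more accurate than it is.

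The separate validation cohort offers no protection. Its labels come from the same process, so the models would be developed and tested against labels that lean the same way. At stake is whether a model that falls short of 75% appears to reach it.

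**Working it through.** **Which read decides.** Each diagnosis is binary, so there are two situations.

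- Nurse and blinded reviewer agree: the final label is one that the unblinded nurse also chose.
- They differ: an unblinded second reviewer chooses.

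Every final label has thus been chosen by at least one unblinded reader. The blinded read can trigger a review but cannot win one on its own.

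**What the second reviewer is not blinded to.** The article does not spell this out. The paragraph raises blinding only because the reference test interacts with some index tests, so the natural reading is that this reviewer may know those index results. The ones the article places at the visit are post void residual and the diary.

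**Where judgement can enter.** Mainly DO, where any filling contraction counts and the question is whether a deflection is a contraction. For BOO and DU, mainly traces near the cut-offs.

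**Size.** The article gives no disagreement rate, so there is no figure to reproduce. What follows is an illustration.

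Inputs from the article (Sample size): prevalence p of 57% (DO), 31% (BOO) and 16% (DU).

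Assumptions:
- sensitivity and specificity are both 70% under blinded adjudication;
- a share d of cases is disputed, independently of the cell of the 2×2 table;
- among disputed cases, a share g of the labels that would contradict the model is moved to agree with it.

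Moving a label shifts a case between the diseased and non-diseased groups: a false negative becomes a true negative, a false positive becomes a true positive. With m = d × g,

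- sensitivity = (TP + m·FP) / (TP + m·FP + FN − m·FN)
- specificity = (TN + m·FN) / (TN + m·FN + FP − m·FP)

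DU with d = 20%, g = 50%, so m = 0.10:

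- TP = 0.16 × 0.70 = 0.112; FN = 0.048; TN = 0.84 × 0.70 = 0.588; FP = 0.252
- sensitivity = (0.112 + 0.0252) / (0.1372 + 0.0432) = 0.1372 / 0.1804 = 76.1%
- specificity = (0.588 + 0.0048) / (0.5928 + 0.2268) = 0.5928 / 0.8196 = 72.3%

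Results as sensitivity/specificity (%), starting from 70/70:

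| d, g | DO | BOO | DU |
|---|---|---|---|
| 5%, 25% | 70.3/70.4 | 70.5/70.3 | 70.8/70.3 |
| 10%, 50% | 71.4/71.6 | 72.0/71.3 | 73.2/71.1 |
| 20%, 50% | 72.8/73.3 | 74.0/72.5 | 76.1/72.3 |

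Both measures rise in every row. DU sensitivity moves most, because at 16% prevalence the relabelled false positives are large relative to the diseased group.

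**Value of m at which 70% appears as 75%.** Setting sensitivity to 0.75 gives m = (0.75·FN − 0.25·TP) / (0.25·FP + 0.75·FN). For DU this is (0.036 − 0.028) / (0.063 + 0.036) = 8.1%. For specificity, m = (0.75·FP − 0.25·TN) / (0.25·FN + 0.75·FP), which for DU is (0.189 − 0.147) / (0.012 + 0.189) = 20.9%. The same formulas give 17.8% and 15.4% for DO, and 12.8% and 19.3% for BOO. At g = 50% the disputed share needed is twice each figure.

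**The case against.** The strongest reply is that a risk is not a result. A reader might infer that the labels do lean towards the predictors and that accuracy is inflated. The article does not support that: it does not say how the second reviewer decides or what material is supplied. It is also possible, though less natural, that non-blinded means only seeing the two discordant reads. A condensed article may leave such detail to the full protocol.

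Several limits stand:

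- The cut-offs are fixed and no index test enters a definition, which narrows discretion for BOO and DU. A dispute may be a plain misread or an artefact rather than a close call.
- A reader might assume that symptom scores also influence the adjudicator. The questionnaires belong to Study Visit Part A, and nothing says the adjudicator sees them. Four Table 1 inputs come from the Flowtaker, which is used at home only after the 3-day call, so the nurse cannot know them at the visit.
- Adjudication is triggered when any of three diagnoses differs, so the disputed share for one condition is at most the share of cases adjudicated.
- Visit context may help to resolve artefact. Removing it could add reading error, which usually lowers apparent accuracy.
- A sensitivity analysis on the blinded read may sit in the analysis plan, which is not shown. Its absence here is no fault.

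That unblinding is part of running urodynamics explains the nurse's position, not the adjudicator's. A blinded reviewer already reads every study, so blinded reading of the recordings is feasible, although this does not prove that blinded arbitration would be equally reliable.

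**Conclusion.** The concern holds as a risk confined to disputed cases. The stated rule lets an unblinded reader overrule the blinded read, and no other section of the article repairs this. The expected direction is upwards for both primary measures in both cohorts; the size cannot be known from the article.

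Under the assumptions above, with 10% to 20% of cases disputed and half of the contradicting labels moved, the shift is 1.1 to 6.1 points. In the 20% case each shift is smaller than the planned precision (for DU sensitivity, 6.1 against 14 points; for DU specificity, 2.3 against 6). Unlike sampling error, however, it is systematic, does not shrink with more men, and can carry a model towards or past 75%.

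A reader might infer one crossing point for all conditions, such as one sixth of cases from 0.05/0.30. That arithmetic holds the denominators fixed, whereas relabelling changes them. Even if every contradicting disputed label were moved, the crossing would run from about 8% (DU sensitivity) to about 21% (DU specificity).

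**What to change.** Have the second reviewer adjudicate from the anonymised trace and the two sets of extracted values, without index-test results, and state this under Review process. If the reviewer is meant to be unblinded only to the two reads, one sentence saying so would settle the point.

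For cases already adjudicated unblinded, repeat the primary sensitivity and specificity with the blinded first reviewer's diagnoses as a sensitivity analysis. Report the disagreement rate between nurse and blinded reviewer for each condition, so that readers can judge how much room for bias there was.

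The cost is small. The adjudication change alters what the reviewer is sent and adds no reads. The sensitivity analysis uses values that the plan already extracts for all studies. No sample size or diagnostic cut-off changes. The downside is that some artefact queries lose visit context. In addition, a single blinded read carries its own reading error, so a lower accuracy in the sensitivity analysis would not be due to review bias alone.
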